# Comparison of intra-articular injections of Hyaluronic Acid and Corticosteroid in the treatment of Osteoarthritis of the hip in comparison with intra-articular injections of Bupivacaine. Design of a prospective, randomized, controlled study with blinding of the patients and outcome assessors

**DOI:** 10.1186/1471-2474-11-264

**Published:** 2010-11-16

## Abstract

**Background:**

Although intra-articular hyaluronic acid is well established as a treatment for osteoarthritis of the knee, its use in hip osteoarthritis is not based on large randomized controlled trials. There is a need for more rigorously designed studies on hip osteoarthritis treatment as this subject is still very much under debate.

**Methods/Design:**

Randomized, controlled trial with a three-armed, parallel-group design. Approximately 315 patients complying with the inclusion and exclusion criteria will be randomized into one of the following treatment groups: infiltration of the hip joint with hyaluronic acid, with a corticosteroid or with 0.125% bupivacaine.

The following outcome measure instruments will be assessed at baseline, i.e. before the intra-articular injection of one of the study products, and then again at six weeks, 3 and 6 months after the initial injection: Pain (100 mm VAS), Harris Hip Score and HOOS, patient assessment of their clinical status (worse, stable or better then at the time of enrollment) and intake of pain rescue medication (number per week). In addition patients will be asked if they have complications/adverse events. The six-month follow-up period for all patients will begin on the date the first injection is administered.

**Discussion:**

This randomized, controlled, three-arm study will hopefully provide robust information on two of the intra-articular treatments used in hip osteoarthritis, in comparison to bupivacaine.

**Trial registration:**

NCT01079455

## Background

Socioeconomic costs have, in general, escalated dramatically in the last ten years [1] with osteoarthritis (OA) being one of the most important causes for this increase. OA is a very common problem in the older population [2,3] and affects almost 5% of people over 65 years of age [4]. OA of the hip is one of the most common causes of functional impairment in the elderly [5,6]. Despite the immense impact of this disease on many people very few effective, non-surgical options are available to handle it. In this regard, (intra-articular) pharmacological treatment is of special interest for two reasons: on the one hand, as basic agent for the relief of pain and pain flares in more acute situations, and on the other, as a way to postpone any surgical intervention by improving the patients' subjective quality of life. In contrast to the knee, the access to the intra-articular compartment of the hip is rather difficult as a result of which injection therapy for hip OA has not been commonly used in the past.

Nowadays, two generally accepted products are used for intra-articular injection in the hip: corticosteroids (CS) and hyaluronic acid (HA). The effects of CS in hip OA have been demonstrated in several controlled studies [7,8]. However its widespread use remains controversial because of its short-term effect and reports of adverse effects following injection [8,9].

The effect of intra-articular HA in the treatment of hip OA has not been fully elucidated. Although studies have shown that HA injections provide prolonged relief from symptoms in patients with knee OA [10-12], some controversy exists over the benefit of HA in the treatment of hip OA. The conclusion of a literature review highlighted the absence of placebo-controlled studies in the treatment of hip OA with intra-articular HA or its derivatives [13]. This means that the role of intra-articular HA in the symptomatic treatment of hip OA cannot be determined conclusively. Nevertheless published data suggest that intra-articular injections of HA in hip OA may be effective. Another literature review showed a relatively low level of evidence of the included studies, although the authors concluded that intra-articular injection of HA, performed under fluoroscopic or ultrasound guidance seems to be an effective treatment and may be an alternative treatment of hip OA [14]. Double-blind, controlled studies with a higher level of evidence are required to confirm these data.

The effectiveness of HA in comparison to CS is also not very clear. One study compared the results of HA with that of CS in patients with hip OA, but a higher number of patients was needed to clarify their conclusion [15]. Most published studies do not have a reliable control group, have too short follow-up periods, or a bias in outcome measure [16,17].

The aim of our randomized, controlled study is to compare the effects of intra-articular injections of HA and CS with a control group, which will receive an intra-articular infiltration with bupivacaine, in patients with painful hip OA. To our knowledge there are no clinical studies which compare the effects of HA, CS and bupivacaine in patients with hip OA.

## Hypothesis

(1) There are differences in functional outcome [differences of more than 10 points using the Harris Hip Score (HHS): [18]] and the Visual Analog Score [VAS: difference of more than 10 mm [19]] between the treatment groups (HA and CS infiltration) and the control group (Bupivacaine) in favour of the treatment groups, at 6 months follow-up in the treatment of symptomatic hip OA patients.

(2) There are differences in secondary outcome measures [Hip disability and Osteoarthritis Outcome Score (HOOS) [20]] between the treatment groups and the control group in favour of the treatment groups, at 6 weeks, 3 and 6 months follow-up in the treatment of symptomatic hip OA patients.

(3) There are differences in functional outcome and the VAS between the treatment groups and the control group in favour of the treatment groups, at 6 weeks and 3 months follow-up in the treatment of symptomatic hip OA patients.

## Methods/design

All patients will be evaluated in the outpatient clinic of our department. After checking the inclusion and exclusion criteria (table 1), eligible patients will be informed about the study and the study design. They will also be well informed about the advantages and disadvantages of participation and the adverse effects of the products. They will be given time to decide if they wish to participate and will be told that their treatment at the centre would not be jeopardized if they declined to participate.

**Table 1 T1:** Eligibility criteria

Inclusion criteria:
1. male and female patients aged between 30 and 70 years
2. pain (VAS) of at least 30 mm on the day of inclusion.
3. radiographic evidence of OA of the hip (Kellgren-Lawrence grading scale 1-3),
4. chronic pain for at least 3 months prior to study entry (day 0),
5. dissatisfaction with previous attempts at non-operative management including nonsteroidal anti-inflammatory drugs.

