**Exclusion criteria:**

1. Kellgren and Lawrence grade 4,
2. an intra-articular hip injection (with any corticosteroid, hyaluronic acid preparation or other) within the previous three months,
3. rapid destructive hip OA.
4. a history of crystalline arthropathy or inflammatory arthritis, neuropathic arthropathy,
5. current other problem in the affected extremity,
6. allergy or hypersensitivity to any of the study medications or to contrast solutions.

Eligible patients that accept to participate will be asked to sign the informed consent form and will be assigned an inclusion number. Approximately 1 month later they will have their treatment (= infiltration).

At day 0 [the day of the infiltration (table 2)] demographic data including age, height, weight, body-mass index (BMI), target hip joint, and the use of nonsteroidal anti-inflammatory drugs will be recorded. The type of treatment the patient will receive will be checked. A nurse working at our day hospital will check the inclusion number and from the internet site http://www.randomizer.org she will, on the day of infiltration, obtain a randomized number ranging from 1 to 3 which corresponds to the treatment injection to be given.

**Table 2 T2:** Flowchart

Day ??	Day of inclusion:	Demographic data, clinical history, concomitant medication, informed consent, inclusion/exclusion criteria.
Day 0	Day of infiltration:	Pain (VAS), HOOS and HHS-score, randomization and infiltration.
Day 1-14	Diary:	Daily VAS and use of pain killers per day.
Week 6	Second consultation:	VAS, HOOS and HHS-score.
Week 12	Third consultation:	VAS, HOOS and HHS-score.
Week 26	Fourth consultation:	VAS, HOOS and HHS-score, end follow-up.

Approximately 315 patients will be included in the study. (see: Planned statistical analysis and sample size calculation).

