### Description of methodology

This is a randomized, masked-observer, controlled trial with three-armed parallel-group design. Patients meeting the inclusion/exclusion criteria will be randomized to one of the following treatment groups:

1. Infiltration of the hip joint with Hyaluronic Acid.

2. Infiltration of the hip joint with Corticosteroids.

3. Infiltration of the hip joint with 0.125% Bupivacaine.

A block randomization scheme, with a block size equal to 8, will be used for the randomization to avoid at random imbalances in group size. No stratification variables are considered in the randomization.

Efficacy parameters will be assessed at baseline and at the planned follow-up visits at 6 weeks, 3 months and 6 months after the injection.

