### Planned Statistical Analysis & Sample size calculation

A linear regression model for repeated measures will be used to compare the evolution of the scores between the groups. More specifically, a direct likelihood approach will be adopted using an unstructured covariance matrix for the repeated measures (Molenberghs and Kenward, 2007, Section 14.4). The approach has the advantage that less stringent assumptions are made, not only with respect to the covariance structure, but also to the mechanism underlying the missing observations. The approach does not assume that all variances or all covariances will be equal (as is done in classical repeated-measures ANOVA or in a mixed model using only a random subject effect). Furthermore, the approach allows that the missingness depends on the observed values (the so-called missing at random assumption (MAR)), whereas an analysis restricted to patients with complete information assumes the missingness to be completely at random (MCAR) (G. Molenberghs and M.G. Kenward)[45].

The primary analysis is based on intention-to-treat, i.e. all patients who received an infiltration at baseline are included. Appropriate transformations will be considered if needed to meet the statistical assumptions of the regression model. Time point-specific comparisons between the groups of the changes with respect to baseline will be made based on this model. Confidence intervals (CI) of the change as well as the difference (at each timepoint) between groups will be constructed. To protect against an inflated type-I error (due to the presence of two outcomes and two pairwise comparisons), an alpha-level of 0.01 will be used for each comparison with respect to the control group (Bonferroni correction).

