A sample size calculation was performed to have at least 80% power to detect in both groups compared with placebo, a clinically meaningful difference in change (baseline-6 months) of 10 mm in VAS and 10 points in HSS. The SD of HSS and VAS is assumed to be equal to 16 and 20 respectively. Estimates are obtained from Frihagen et al. [46] and Qvistgaard [15]. Assuming a moderate correlation of 0.5 between the measurement at baseline and after 6 months, a total of 285 patients are needed, i.e., 95 subjects in each group. With this sample size, 80%power is achieved for VAS and 96.2% for HHS. The number of included subjects will be increased by 10% to compensate for the loss of power due to patients with missing observations (therefore, 105 patients per group will be recruited). Interim analyses are planned after 1/3 and 2/3 of the patients included reach the end of the follow-up period to allow for an early stopping of the study (or accrual of patients in a specific treatment group) due to rejection of the null hypothesis. Using the O'Brien-Fleming method (O'Brien and Fleming 1979) results in respectively |4.495|, |3.178| and |2.595| as critical values for the Z-statistic at the three analysis time points. Otherwise stated, p-values are declared significant if they reach p < 0.000007, p < 0.00148 and p < 0.0095 at the first interim analysis, the second interim analysis and at the final analysis, respectively. (Note that the 'price to pay' for performing the interim analysis is a slightly more conservative alpha-level at the final analysis, i.e. alpha = 0.0095 instead of alpha = 0.01)

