#### Secondary outcomes

Assessment of group differences on:

• Hip disability and Osteoarthritis Outcome Score (HOOS) [20]: this score will be used as a self-administered questionnaire with the help of the developers' instructions. The HOOS is an adaptation of the Knee disability and Osteoarthritis Outcome Score (KOOS) intended to evaluate symptoms and functional limitations related to the hip. The HOOS consists of 40 items assessing five different patient-relevant groups: Pain (P) (ten items); Symptoms (S) including stiffness and range of motion (five items); Activity limitations-daily living (A) (seventeen items); Sport and Recreation Function (SP) (four items); and Hip Related Quality of Life (Q) (four items). The HOOS contains all Western Ontario and McMaster Universities Osteoarthritis Index (WOMAC) questions in unchanged form. The WOMAC scores are often used in scientific literature and it is important that if needed the WOMAC scores can be calculated from the HOOS questionnaire. To answer each question, five options are used (no, mild, moderate, severe, extreme). All items are scored from zero to four, and each of the five subscales will be calculated as the sum of the items included. The HOOS is transformed into a 0-100 worst to best score.

• VAS, Harris Hip Score: at all follow-up time points, except after 6 months

• Patient evaluation of treatment outcome: The patients will be asked to assess their status on a 3-point scale (worse, stable or better then at the time of enrollment).

• Intake of escape medication: The number of escape medication taken/day will be determined.

• Safety: All complications/adverse events will be evaluated and the relationship to the test product determined. When they have complications, patients will be seen in our department earlier than normal.

The above primary and secondary measure instruments will be assessed at the time of enrollment into the study prior to any injection (baseline), and then again at six weeks, 3 and 6 months after the injection. The six-month follow-up period for all patients will begin on the date the injection is administered.

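### The primary VAS contrast rests on change from one baseline; common-mean use of the pre-randomisation readings would sharpen it, mostly through day 0 and only slightly through the inclusion-day reading

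*Protocol article*

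**What the plan says.** In Methods/design, Table 1, the second inclusion criterion is "pain (VAS) of at least 30 mm on the day of inclusion". The text after the exclusion criteria then says "Approximately 1 month later they will have their treatment (= infiltration"). For day 0, Table 2 lists "Pain (VAS), HOOS and HHS-score, randomization and infiltration". A VAS is therefore implied at inclusion and scheduled on day 0, and both precede allocation.

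The efficacy analysis has one pre-treatment occasion. Description of methodology states: "Efficacy parameters will be assessed at baseline and at the planned follow-up visits at 6 weeks, 3 months and 6 months after the injection". The analysis model is set out in the section Planned Statistical Analysis & Sample size calculation: it is a direct-likelihood repeated-measures model with unstructured covariance, and the section adds: "Time point-specific comparisons between the groups of the changes with respect to baseline will be made based on this model". The sizing targets "a clinically meaningful difference in change (baseline-6 months) of 10 mm in VAS and 10 points in HSS", with one correlation of 0.5 between baseline and month 6. It reports 80% power for VAS and 96.2% for HHS, so VAS determines the sample size.

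Secondary outcomes says the instruments "will be assessed at the time of enrollment into the study prior to any injection (baseline"), whereas Table 2 puts the first scheduled scores on day 0. The two places differ on which day is baseline, but under either only one reading enters the contrast.

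**The concern.** A single VAS mark is a noisy baseline: the plan itself assumes that it correlates only 0.5 with month 6. At that correlation, subtracting the baseline in full gains nothing over analysing the month-6 value alone, because the variance of the change equals the variance of one reading. Randomisation makes the expected pre-injection means equal across arms. A model that uses this fact weights the baseline information efficiently and does not bias the group difference. At stake is the width of the confidence interval for the primary outcome with less power, at no cost in patients or visits.

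**Working it through.** **Inputs from the sample size section.** VAS SD 20 ("The SD of HSS and VAS is assumed to be equal to 16 and 20 respectively"), difference 10 mm, day-0-to-month-6 correlation 0.5, 95 per arm, final critical value 2.595.

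**Assumptions, not in the documents.** The inclusion VAS also has SD 20. Its correlation with day 0 is r, shown from 0.5 to 0.9. Its correlation with month 6 is c, shown from 0.3 to 0.5.

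**Formula.** With variance factor f relative to SD², SE = 20·√(2f/95) and power = Φ(10/SE − 2.595).

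**1. The plan's figure.** For change from one baseline, f = 2(1 − 0.5) = 1.00. SE = 2.90 mm, 10/SE = 3.446, power = Φ(0.851) = 80.3%. This reproduces the stated 80%, so the trial is sized on a change score from one reading.

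**2. Day 0 alone, mean common to the arms (or as a covariate).** f = 1 − 0.5² = 0.75. SE = 2.51 mm, 10/SE = 3.979, power = Φ(1.384) = 91.7%.

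**3. Both readings, means common to the arms (or as two covariates).** f = 0.75 − (c − 0.5r)²/(1 − r²).

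| r | c | f | Power | Variance saved beyond step 2 |
|---|---|---|---|---|
| 0.5 | 0.5 | 0.667 | 94.8% | 11% |
| 0.5 | 0.4 | 0.720 | 92.9% | 4% |
| 0.5 | 0.3 | 0.747 | 91.8% | under 1% |
| 0.7 | 0.5 | 0.706 | 93.4% | 6% |
| 0.7 | 0.4 | 0.745 | 91.9% | under 1% |
| 0.7 | 0.35 | 0.750 | 91.7% | 0 |
| 0.8 | 0.4 | 0.750 | 91.7% | 0 |
| 0.9 | 0.5 | 0.737 | 92.2% | 2% |

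The gain is zero when c = 0.5r, that is, when inclusion predicts month 6 only through day 0. If c falls below 0.5r, the formula again shows a gain, but through a negative weight on the inclusion reading. At r = 0.9 and c = 0.3 this gives f = 0.632. I do not count that corner: two nearly identical readings would have to differ by 0.2 in their correlation with month 6.

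**4. Change from the plain mean of the two readings.** f = 1 + (1 + r)/2 − (0.5 + c).
- r = 0.5 and c = 0.5, 0.4, 0.3: f = 0.75, 0.85, 0.95; power 91.7%, 87.3%, 82.7%.
- r = 0.7 and c = 0.3: f = 1.05; power 77.9%, below the planned design.

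**5. Selection at 30 mm.** A simulation truncated the inclusion VAS at 30 mm (underlying mean 45 to 65, SD 20, r 0.5 to 0.7, both correlations with month 6 equal to 0.5 before truncation). Residual variance with both readings as covariates was 4% to 10% below that with day 0 alone, so truncation does not remove the gain in those settings.

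**The case against.** The strongest reply is that nothing here is wrong. The stated sample size reproduces, the contrast is unbiased, and a condensed article may leave the handling of a screening value to the analysis plan. The model class that it names does not exclude common pre-randomisation means or an extra occasion. That stands, and it limits the point to a recommendation. The article does, however, state the contrast and a sizing that corresponds to f = 1.00, so the comment addresses what is written.

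A reader might infer that the second reading lifts power from 80% to 92–95%. The figures do not support that: day 0 alone, handled with a common mean, already gives 91.7%. A reader might also infer that any use of both readings helps; step 4 shows that averaging can lose power.

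Three further limits stand:
- Table 2 does not list VAS by name on the inclusion day. The criterion implies a reading, but no passage says that its millimetre value is kept as study data.
- The larger gains need readings one month apart to correlate no better than readings six months apart. A higher r with a lower c is quite natural and leaves little or nothing.
- HHS has no scheduled inclusion-day score, so the two primary outcomes would have slightly different models.

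None of these defeats the proposal. The likelihood weights the inclusion reading by what it contributes, so a weak reading costs only a few covariance parameters.

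**Conclusion.** The point holds as an optional improvement in precision. On the plan's own SD, correlation, sample size and final limit, common-mean treatment of day 0 cuts the variance of the VAS contrast by 25% (power 80.3% to 91.7%). The inclusion reading adds 0 to 11% of the remaining variance, about 0 to 3 power points. That second figure rests on assumed correlations (r 0.5 to 0.9, c 0.3 to 0.5, apart from the negative-weight corner noted above) and on equal SDs. The power figures use the normal approximation and complete data at 95 per arm. The documents do not support a stronger reading, namely that the plan is biased, wrongly sized, or forgoes a large gain by leaving out the inclusion-day VAS.

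**What to change.** State in the analysis section that the inclusion-day VAS is recorded in millimetres. State also that the inclusion and day-0 values enter the planned unstructured-covariance VAS model as pre-randomisation occasions, with each mean common to the three arms (or, equivalently in purpose, as two covariates). Report the 6-month group differences from that model. Keep day 0 as the reference for within-arm change, because selection at 30 mm raises the inclusion value, and align the baseline wording in Secondary outcomes with Table 2. Do not use the plain mean of the two readings as the baseline.

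If the inclusion value cannot be stored, apply the common-mean form to day 0 alone, which keeps most of the gain.

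Costs: the covariance matrix grows from 10 parameters (4·5/2) to 15 (5·6/2), which is minor with about 300 patients; the value must be stored rather than ticked off; and the VAS model has one more occasion than the HHS model. No extra patients or visits are needed.

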**Exclusion criteria:**

1. Kellgren and Lawrence grade 4,
2. an intra-articular hip injection (with any corticosteroid, hyaluronic acid preparation or other) within the previous three months,
3. rapid destructive hip OA.
4. a history of crystalline arthropathy or inflammatory arthritis, neuropathic arthropathy,
5. current other problem in the affected extremity,
6. allergy or hypersensitivity to any of the study medications or to contrast solutions.

Eligible patients that accept to participate will be asked to sign the informed consent form and will be assigned an inclusion number. Approximately 1 month later they will have their treatment (= infiltration).

At day 0 [the day of the infiltration (table 2)] demographic data including age, height, weight, body-mass index (BMI), target hip joint, and the use of nonsteroidal anti-inflammatory drugs will be recorded. The type of treatment the patient will receive will be checked. A nurse working at our day hospital will check the inclusion number and from the internet site http://www.randomizer.org she will, on the day of infiltration, obtain a randomized number ranging from 1 to 3 which corresponds to the treatment injection to be given.

**Table 2 T2:** Flowchart

Day ??	Day of inclusion:	Demographic data, clinical history, concomitant medication, informed consent, inclusion/exclusion criteria.
Day 0	Day of infiltration:	Pain (VAS), HOOS and HHS-score, randomization and infiltration.
Day 1-14	Diary:	Daily VAS and use of pain killers per day.
Week 6	Second consultation:	VAS, HOOS and HHS-score.
Week 12	Third consultation:	VAS, HOOS and HHS-score.
Week 26	Fourth consultation:	VAS, HOOS and HHS-score, end follow-up.

Approximately 315 patients will be included in the study. (see: Planned statistical analysis and sample size calculation).

Injection of the study drugs will be performed under sterile conditions by the same experienced orthopaedic surgeon and senior author [name] in all patients. After skin cleaning a lumbar puncture needle is inserted in a lateral approach. Layer by layer local anaesthesia is performed using lidocaine 1%. Arthrocentesis is carefully performed prior to each injection to remove any effusion. Iodinated contrast agent Ultravist^® ^(Schering, Berlin, Germany) will be injected. The needle positioning into the joint cavity will be fluoroscopically controlled when the contrast is injected. When the needle is in the correct position the injection will be performed. Another option to perform the injection in the hip is using ultrasound [21,22]. The skin is cleaned and a lumbar puncture needle is inserted in an anterior approach. Layer by layer local anaesthesia is performed using lidocaine 1%. Arthrocentesis is performed followed by the injection of the assigned study product. After resting for 2 hours, the patient is allowed to walk and to return home. The patient is advised to rest at home until the next morning. Oral symptomatic slow acting drugs for OA (for example glucosamine and chondroitin) are authorized if they are taken at a stable dose for more than 3 months prior to inclusion in the study. These drugs are continued at a stable dose during the study treatment period.

There will be 3 different groups of treatment:

1. Infiltration of the hip joint with Hyaluronic Acid (Ostenil plus 40 mg/2ml).

2. Infiltration of the hip joint with Corticosteroids (Depo-Medrol 80 mg/2ml).

3. Infiltration of the hip joint with 0.125% Bupivacaine (0.125% Marcaine 2 ml).

All the products used in this study are already used in our department. To date, we have never had problems using these products.

"Post-injection" data collection will be performed by a person who is blinded to the treatment received by each patient and who is skilled in the administration of the study outcome instruments.

There will also be a diary to be filled in by each included patient for the first two weeks after the infiltration to assess if the treatments have an effect on hip OA. The diary will include a VAS scale (0-100 mm) for each day. Patients will be required to fill in their VAS score and also the number of pain killers used each day. Side effects will also be reported.

In summary we can conclude that both the patient and the person who will collect the "post-injection" data will not know which kind of infiltration the patient has received.

The findings on the initial radiographs will be graded by a musculoskeletal radiologist, experienced in reviewing orthopedic X-rays using the Kellgren and Lawrence grades.

